## Abstract

**Background-:**

Hospital acquired infections are a major cause of morbidity and mortality and markedly increased health care costs. Critically ill patients who require management in an Intensive Care Unit are particularly susceptible to these infections which are associated with a very high mortality. Selective decontamination of the digestive tract (SDD) may reduce these infections and improve mortality but it has not been widely adopted into practice. We aim to 1. Clarify reasons why clinicians have avoided implementing SDD into clinical practice despite the current best-evidence 2. Describe barriers to SDD implementation and 3. Identify what further evidence is required before full scale clinical implementation would be considered appropriate and feasible.

**Methods-:**

We have developed an international 'multi-lens' approach to investigate SDD from several perspectives. In case studies we will identify accounts of implementation of SDD in practice, in terms of the behaviours performed by the full range of individual clinicians, accounts of how SDD was first introduced into the Unit and specific content that may be used to populate the content of behaviour change techniques to be used in an implementation intervention and procedures to consider in order to deliver an implementation trial. In a 4 round Delphi study we will identify the range of stakeholders' beliefs, views and perceived barriers relating to the use of SDD. We will generate hypotheses about key beliefs about SDD and will inform the feasibility of any future randomised controlled trial. In large-scale nationwide postal questionnaire surveys of the state of current practice we will identify the factors predicting acceptability of an effectiveness or implementation trial using, and informed by, the theoretical domains structure. In semi-structured interviews with active international clinical trialists we will assess the feasibility of a randomised controlled trial and identify challenges and barriers to undertaking research in the field of SDD research.

**Discussion:**

We believe these methods will allow us to determine whether clinical implementation trials or further large effectiveness trials are required before full scale implementation into clinical practice.

## Background

Each year in the UK 140,000 patients are admitted to an intensive care unit (ICU) and of these almost 60,000 will die within a year of admission. Hospital acquired infections (HAI) are a major clinical problem for modern health services as they are associated with morbidity and mortality as well as high additional health care costs. Critically ill patients are extremely susceptible to HAI and these are associated with a high additional mortality, prolonged hospital stays and a large health care resource utilisation. Between 20 and 50% of ICU patients suffer from such infections and major efforts are being undertaken to improve these outcomes [1,2].

An intervention that has gained much interest in reducing HAI is selective decontamination of the digestive tract (SDD). SDD involves the application of topical non-absorbable antibiotics to the oropharynx and stomach and a short course of intravenous antibiotics [3-14]. The evidence base relating to SDD is reasonably strong with 12 meta-analyses of 28 randomised controlled studies in the literature [3-14]. Ten of these studies demonstrate a benefit in terms of reducing pneumonia rates and six studies show a specific mortality benefit in all ICU patients or in major subgroups [3]. A very recent large cluster randomised study from the Netherlands demonstrated a 3.5% reduction in adjusted mortality associated with SDD [14]. Problems with these meta-analyses include clinical heterogeneity, lack of blinding and lack of data on compliance with intervention. The Cochrane review of SDD demonstrated an association with reduction in pneumonia, OR 0.32 (0.26-0.38) and death OR 0.75 (0.65-0.87)[3]. None of the published meta-analyses included the recent cluster randomised study [14]. This mortality benefit was present in the more recent randomised studies and is of the magnitude of 3-6% absolute risk reduction (ARR) with a number needed to treat (NNT) of approximately 17 to save one life [3,14]. If this mortality benefit could be realised in UK practice then it could save as many as 2-3000 lives per annum. However, these findings require to be confirmed in other health care environments.

Despite this evidence base, ICU practitioners have not widely adopted this intervention with only 10-15 ICUs (out of 240) reporting that they undertake SDD in the UK [14,15]. Existing surveys of practice have been unable to fully elucidate the reasons for this lack of adoption and implementation [14,15]. Reasons may include fears over encouraging antibiotic resistance, a lack of biological plausibility for the findings and a lack of external validity of the evidence base since most of the existing studies come from countries where infections due to multi-resistant organisms are uncommon [14]. Finally, it is possible that this intervention is so counterintuitive that clinicians will not change their practice regardless of the evidence base or that one clinician group could impede another group, who are in favour of the intervention, from implementing it.

It seems that until there is high quality evidence demonstrating clinical effectiveness, cost-effectiveness and the ecological impact of SDD in a range of health care systems, this intervention is unlikely to be implemented and thus patients will be denied a potentially life saving therapy. However, despite the clear importance of HAI in critically ill patients, and despite a multi-national appreciation and prioritisation of the importance and urgency of this research topic, it remains unclear why this intervention has not been implemented. Little is known about clinicians' beliefs about the existing evidence base, the perceived benefits and risks of SDD in clinical practice, the factors that influence current practice and likely barriers to implementation. Further, it is also unclear whether there is a requirement for further high level evidence of effectiveness before implementation would become acceptable and what sort of study would be feasible and acceptable to clinicians and trialists. This multi-method study will address these issues in three regions (the UK, Canada and Australia/New Zealand).

## Aims

The overall aim of this study is to identify the perceived risks, benefits and barriers to the use of SDD in critical care units. To achieve this aim, the following objectives are proposed (with formal research questions (RQs) listed):

1. To identify and precisely describe the clinical intervention in units and hospitals that deliver SDD:

• **RQ1**: What are the components of the intervention of SDD?

• **RQ2**: How has SDD been implemented and delivered into practice?

2. To identify the range of beliefs, interpretation and views about the current evidence base relating to the use of SDD in key stakeholder groups:

• **RQ3**: What are the views of key stakeholders about the likely positive and negative consequences of implementing SDD in ICUs?

• **RQ4**: What are the views of key stakeholders about the likely *barriers *to implementing SDD in ICUs?

• **RQ5**: What are the views of key stakeholders of the internal/external validity and adequacy of the existing evidence base for SDD?

3. To identify current practice and assess the acceptability of further randomised controlled trials in the field of SDD in a wide group of intensive care clinicians and infectious disease clinicians/medical microbiologists:

• **RQ6**: What are the current practices and intentions of intensivists and infectious disease clinicians/medical microbiologists about SDD?

• **RQ7**: If there are uncertainties in the evidence base, do these clinicians believe they could be addressed in a clinical trial and what research questions, trial design(s) and interventions would be optimal and what predicts these beliefs?

4. To assess the feasibility of a proposed effectiveness randomised controlled trial comparing SDD against a control group in ICUs among international intensive care clinical trialists:

• **RQ8**: What are the likely challenges in undertaking a large multi-national randomised controlled study of SDD in ICU?

## Methods

The study will use a 'multi-lens' approach to investigate SDD from several perspectives and in three national regions (the UK, Canada and Australia/New Zealand) to allow greater understanding and international comparisons of the issues that relate to the implementation of this therapy. The investigation will involve four inter-related stages (Figure 1 shows a schema of this study).

**Figure 1 F1:**
[figure not shown]
Design of study showing links to research questions

### Stage 1

#### Case studies will be conducted in units in which SDD has been implemented (targeting RQs 1 and 2)

This stage will be conducted only in the UK region as there are no adult critical care units in the other regions who use SDD. The case studies will focus on a behavioural analysis of the processes of implementation, based on a modification of Michie and Johnston's [16] advice for specifying clinical behaviour (who, what, to whom, when, how). It will identify the "A,B,C" (antecedents, behaviour, consequences)[17] of each action that is taken in the sequence of behaviours between identifying a patient who may be eligible for SDD, prescribing, supplying, storing, communicating, administering (to the patient) and so on, and the factors associated with the 'flow' between these actions. This will involve observational visits, interviews with a range of clinical staff (e.g. consultants, registrars, pharmacists, nurses etc) and documentary analysis, which will be used to identify the actions required from all staff to (a) introduce SDD to the ICU and (b) maintain, regulate and optimise the delivery of SDD over time. These case studies will inform the practical issues around implementation of SDD in ICUs either in the context of a trial intervention or to inform implementation strategies. Two SDD units will be purposively sampled from an existing database from a national survey of SDD in the UK [15]. One Unit that has recently implemented SDD and one that has used SDD over a longer period will be identified. When identified, SDD Units will be contacted and asked to take part in the study. From multiple visits to each site, structured observations of the administration of SDD in the ICU will be followed by semi-structured interviews with nursing staff, clinical leads and other decision makers to elicit accounts of the processes of change, including decision making, documentation and resource issues. Retrospective accounts will be elicited, describing how the Unit decided to introduce SDD, factors that triggered change, barriers experienced (i.e., interruptions to the 'flow' of actions), and the strategies used to overcome them. The perceived consequences of the SDD policy for the unit (and the hospital more generally) will be documented.

The case studies will identify accounts of implementation of SDD in practice, in terms of the behaviours performed by the full range of individual clinicians; accounts of how SDD was first introduced into the Unit; specific content that may be used to populate the content of behaviour change techniques to be used in an implementation intervention and procedures to consider in order to deliver an implementation trial.

### Stage 2

#### A Delphi study to identify the range of stakeholders' beliefs, views and perceived barriers relating to the use of SDD (targeting RQs 3, 4,5 and 7)

This stage will be conducted in all three regions. This phase of the investigation will generate hypotheses about key beliefs about SDD and will inform the feasibility of any future randomised controlled trial. Using a Delphi technique comprising an initial exploratory 'round' so that the full range of views may be raised and then considered by all participants in later rounds, followed by three iterations (i.e. four rounds in all), we will sequentially build a picture of respondents' beliefs and views on SDD. We will further assess the likely factors influencing the acceptability of any future randomised controlled trial comparing SDD against a control group (not including SDD) in ICUs and/or a proposed randomised controlled trial comparing implementation strategies for SDD against a control group in ICUs. Rounds 1 to 3 will be conducted independently within each region, whilst round 4 will be multi-region.

There is a broad range of estimates of suitable sizes for a Delphi panel, but smaller sizes (such as 10 per stakeholder group) have been deemed appropriate where panel members have similar training [18]. Four key stakeholder clinician groups (ICU physicians, ICU pharmacists, infectious disease clinicians/medical microbiologists, ICU clinical managers) will be sampled using existing databases from within each region. We will aim for 10 from each stakeholder group. The total sample size will thus be approximately 40 in each of the three regions. Purposive diversity sampling will be used in all groups to identify as wide a range of initial views as possible, based on a range of variables: Academic-affiliated or not; years of experience (time since commencing as consultant/other professional grade); size of ICU (i.e. number of ICU beds); and current practice (routinely perform SDD or not). During the interview phase, diversity on these factors will be tracked using a diversity sampling table and additional participants will be invited to participate, if required, to maximise variation. Transcribed interviews will be content analysed based on the theoretical domains framework using methods previously employed by the research team in the context of critical care [19].

The Delphi study report will present (i) the perceived importance of each specific belief about the use of SDD in ICUs; (ii) the acceptability and feasibility of conducting an effectiveness trial; and (iii) the acceptability and feasibility of conducting an implementation trial. In round 4, the data from each regional setting will be presented to all international participants by email. The international comparisons in this round are important, to increase the generalisability of the results and of any future study result, since lack of generalisability may have been a major factor limiting the uptake and implementation of SDD in the past. This round will require that the investigations conducted in each country use a broadly parallel time frame, so that the feedback is presented to all participants with similar time intervals. The full Delphi results will allow us to consider how best to elaborate the key findings from the nationwide survey of the state of current practice, described below.

### Stage 3

#### Nationwide surveys of the state of current practice to identify the factors predicting acceptability of an effectiveness or implementation trial (targeting RQs 6 and 7)

This stage will be conducted in all three regions using large-scale postal questionnaire surveys using existing databases of intensivists and infectious disease clinicians/medical microbiologists in each region. This questionnaire design will be informed by the theoretical domains structure [17] but only the domains identified in the Delphi study as relevant to implementation of SDD will be included. Questionnaire items will be developed using standard theory-based methods with a 7-point response format [20]. The exact content of the questionnaire will be informed by the specific beliefs and views identified as important in the Delphi, thereby ensuring maximum relevance. The draft questionnaire (and cover letter) will be pilot tested using one-to-one interviews with 4 clinical collaborators to assess wording, acceptability and length. An appropriate course of action will then be agreed (i.e. accept, change, eliminate etc). Reminder letters (up to a maximum of two) will be posted to non-responders at two-week intervals after the first posting. Analysis will include simple descriptive and statistical prediction techniques [21-24]. These surveys will attempt to establish the current state of practice in ICUs with regard to SDD, the nature of evidence still required and perceived barriers to implementation of SDD. In addition, they will identify the willingness of intensive care clinicians to participate in any future effectiveness trial of SDD in intensive care practice and/or an implementation trial of strategies to increase uptake. The strongly predicting constructs and variables will be targeted if this programme progresses to an implementation trial, using systematic methods for intervention development [22].

### Stage 4

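### The survey's domain filter names only relevance to implementing SDD, so predictors specific to accepting or joining a trial may be left out of the prediction part of RQ7

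*Protocol article*

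**What the plan says.** The Stage 3 heading (Methods) gives the survey's purpose as "to identify the factors predicting acceptability of an effectiveness or implementation trial" and assigns it RQs 6 and 7. The last part of RQ7 (Aims) asks "what research questions, trial design(s) and interventions would be optimal and what predicts these beliefs", where the beliefs concern whether and how a trial could settle the uncertainties about SDD.

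The Stage 3 text bases the questionnaire on the theoretical domains but restricts them: "only the domains identified in the Delphi study as relevant to implementation of SDD will be included". A later sentence adds: "The exact content of the questionnaire will be informed by the specific beliefs and views identified as important in the Delphi". The survey will also measure willingness to join a future effectiveness or implementation trial.

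Stage 2 (the Delphi study) has a wider remit than implementation. It also targets RQ7, and it states: "We will further assess the likely factors influencing the acceptability of any future randomised controlled trial comparing SDD against a control group". Its report lists three outputs: (i) how important each belief about using SDD is thought to be, then "ii) the acceptability and feasibility of conducting an effectiveness trial", and (iii) the same for an implementation trial.

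Outcome of project treats two intentions separately. Five result patterns turn on intention to implement SDD, four of them together with what predicts it. A second list turns on whether willingness to participate in a trial is low or high, and adds scores for how easy or hard participation is thought to be.

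**The concern.** The domains are selected for one behaviour, using SDD, and then serve to explain another, accepting or joining a trial. Some drivers may matter for both. Others, such as research capacity, views on randomising a whole unit, or consent, could bear on a trial without bearing on routine use. If such drivers fall in a domain that the Delphi does not link to implementation, the filter as worded keeps that domain off the questionnaire.

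What is at stake is how willingness to participate is explained. A model without trial-specific predictors could not show, from survey data, whether low willingness reflects beliefs about SDD or features of the trial. Retained SDD beliefs that correlate with omitted trial beliefs would carry part of their association. Questions that were not asked cannot be recovered once the forms have been posted.

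**Working it through.** The plan states no figure on this point, so the check is a comparison of texts.

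1. **Outcome to be predicted.** The Stage 3 heading and the end of RQ7 both name trial acceptability or beliefs about a trial.
2. **Admission rule for predictors.** The one stated criterion for a domain is relevance to implementing SDD, and it is worded as an exclusion (*only*).
3. **Are the two behaviours the same in this plan?** No. Outcome of project scores intention to implement and willingness to participate separately, with different rules for each. For an implementation trial the two are close, so the gap concerns mainly the effectiveness trial.
4. **Is the missing material collected?** Yes. Stage 2 elicits the factors that influence trial acceptability. The domain clause does not say that they pass to the questionnaire.
5. **Does the later content sentence admit them?** Not clearly. It refers to beliefs found important in the Delphi, but the Delphi report attaches importance ratings to beliefs about using SDD (item i) and lists trial acceptability separately (items ii and iii). A sentence on what informs content does not plainly override *only*.
6. **Could another stage supply the prediction?** No. The Delphi has 4 groups × 10 = about 40 purposively sampled people per region, and Stage 4 seeks 10 trialists and targets RQ8. Both can describe views. Stage 3 is the only stage for which statistical prediction is planned.
7. **Do the decision rules use the affected quantity?** No. The predictor-based patterns concern intention to implement, and willingness enters by its level only.

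**Can a size be given?** Only by assumption. With standardised variables, one retained belief (true effect *b*), one omitted belief (true effect *c*) and correlation *r* between them, the apparent effect of the retained belief is *b* + *r* × *c*. None of these values is in the documents. Taking *c* = 0.45 purely for illustration:

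| Assumed *b* | *r* = 0.2 | *r* = 0.6 | Apparent ÷ true |
|---|---|---|---|
| 0.10 | 0.10 + 0.09 = 0.19 | 0.10 + 0.27 = 0.37 | 1.9 to 3.7 |
| 0.30 | 0.30 + 0.09 = 0.39 | 0.30 + 0.27 = 0.57 | 1.3 to 1.9 |

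The ratio is set by the chosen *b*, and at *r* = 0 there is no distortion of the retained effect at all. The table shows a mechanism and does not estimate a bias for this survey.

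**The case against.** The strongest reply is that the clause is loose wording with little effect. Four parts of that reply stand.

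- **The filter acts on broad domains, not on items.** Nothing shows that research capacity, randomisation or consent would fall in a discarded domain. Outcome of project already expects constructs for social influence and capacity, so those areas are likely to be covered. A reader might infer that trial-specific drivers are bound to be removed; the text supports only that they may be.
- **Some trial-specific content is expected.** The score for ease or difficulty of participating is one example. It is named as an input to the decision, but once measured it could also serve as a predictor.
- **RQ7 is wider than its last clause.** A reader might infer that RQ7 cannot be answered. That goes too far: Stage 2 also targets RQ7, and whether a trial could resolve the uncertainties, and which questions and designs are best, can be described without the domain filter.
- **Trial design issues are examined elsewhere.** Outcome of project takes practical, ethical and design issues from the Delphi and the case studies, and Stage 4 asks trialists about cluster randomisation, recruitment and ethics. A reader might infer that the go/no-go decision is distorted, but no listed rule uses predictors of willingness.

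It can also be said that a condensed article leaves the final questionnaire to the full protocol and to Delphi results not yet available. That would answer a complaint about missing detail. Here the article states an exclusion rule, and that rule does not match the stage's own purpose.

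**Conclusion.** The mismatch is real and limited in reach. As worded, the domain rule may leave out domains relevant to joining a trial, mainly the effectiveness trial, that are not relevant to using SDD. The part of RQ7 that asks what predicts beliefs about a trial could then be answered from an incomplete predictor set, in the only stage that plans statistical prediction.

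The conclusion assumes that the clause is applied literally and that the Delphi finds at least one domain tied to trial participation but not to implementation. If either fails, nothing is lost. No size of bias can be given from the documents. The point is worth correcting before the questionnaire is finalised, because the edit is small and omitted items cannot be added after posting.

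**What to change.** In Stage 3, extend the domain clause so that, after relevance to implementing SDD, it continues: *or to acceptability of, or participation in, an effectiveness or implementation trial*. Then state that the trial-relevant domains are candidate predictors of willingness to participate. If the team already intended this, the edit only makes the intention explicit.

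The cost is one clause and a few extra items, hence a slightly longer form. The planned pilot interviews already assess length, and the Delphi data needed to choose the items are already due to be collected.
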